## Methods/Design

### Study design

This level II observational prospective cohort study, executed in 4 different Dutch hospitals, will include all subsequent patients visiting the Emergency Department (ER) reporting for a first-time sustained ankle inversion injury. These patients will be asked to fill out a questionnaire at 2 weeks, 3-, 6- and 12 months after their ankle sprain of which only the 12 month follow-up questionnaire is mandatory to diagnose CAI.

The study design (Fig. 1) is in accordance to the principles of the Declaration of Helsinki (version 10, October 2013 by 64th WMA General Assembly, Fortaleza, Brazil) and in accordance with the Medical Research Involving Human Subjects Act of the Netherlands. The study is approved by the local institutional review board (IRB) of the Academic Medical Center (AMC) and Flevoziekenhuis (W16_258 # 16.303), the Slotervaart Medical Center (U/16.130/P1654) and the VU Medical Center (VUmc) (2016.541).

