#### Follow-up

A legally required waiting period of two weeks is observed prior to asking consent and sending the questionnaires to the patient’s home address or email address. Patients are asked to fill out the first questionnaire immediately which gives a T0 (baseline measure at approximately two weeks after the initial sprain). The subsequent evaluation time points are T1 interim evaluation after three months, T2 after six months, and T3 at twelve months. The questionnaires contain questions about patient characteristics, previous ankle sprains, treatment, restrictions and complaints. Additionally the questionnaires contains the Foot and Ankle Outcome Score (FAOS) and the Cumberland Ankle Instability Tool (CAIT) to evaluate recovery. To ensure all patients with CAI are identified, one year after their ER visit they will be contacted, inquiring on persisting complaints and ankle instability. Patients that indicate on the first questionnaire they sustained ankle sprains prior to their ER visit will not receive further follow-up questionnaires, as these patients are considered to have CAI and therefore need no extra monitoring to identify whether they develop CAI or not. They will not be included in the primary analysis as this may lead to overfitting of the current model. Concomitant neuromuscular adaptations and additionally may follow a different rehabilitation route due to familiarity with the complaints.

In case of persisting complaints six months after the ER visit, patients will be eligible for surgical treatment according to Dutch standards. This is to avoid unnecessary invasive treatment on patients as a large proportion recover by means of conservative treatment [7].

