#### Additional analyses

By comparing PROM scores over time, overall recovery will be assessed. In addition, the different treatments and symptoms during physical examination will be assessed for their relation to the functional outcome, as measured by the FAOS and CAIT and persisting complaints of instability. The final sub-analysis differentiates between the amount of recurrent ankle sprains prior to the initial ER visit to check whether the model is also applicable on patients that already suffer from CAI, as identified by the first questionnaire.

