### Data analysis and statistics

Demographics of the study population will be analyzed using the descriptive statistics. All statistics will be performed with SPSS version 23.0 (SPSS Inc., Chicago, IL, USA) and R package ‘Stats’ version 3.3.3 (University of Auckland, Auckland, New Zealand). A *p*-value of < 0.05 is considered significant. Normality of data will be assessed using the Shapiro-Wilks test.

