#### Prognostic value of variables

Depending on normality of data the Pearson or Spearman correlation coefficients will be used to assess correlations. A scatterplot for numerical data and Odds Ratio (OR) for binary data will be used to provide additional information on possible correlations in the data between prognostic factors. In case of correlations (*p* < 0.10 to avoid overfitting [40]) shown by an univariate analysis, a multivariate logistic regression will be performed to assess dependency between variables. The R^2^ will be used to visualize model fitness for the contribution of a factor to the progression to CAI and for the full model.

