#### Additional analyses

To assess overall recovery, mean and Standard Deviation (SD) of the functional outcome scores are calculated using the paired T-test. In case of skewed data the Wilcoxon signed rank test will be used instead, reporting the median and range.

To assess whether the received treatment affects functional outcome and/or the progression to CAI will be assessed. Depending on normality of data the Pearson’s or Spearman’s rho will be used.

Finally based on the amount of ankle sprains experienced prior to participation in this study, patients will be defined as suffering from an acute lateral ankle sprain (LAS) or CAI. The correlation coefficient of acute LAS and bone geometric factors, and CAI and bone geometric factors will be calculated using the Pearson’s or Spearman’s rho (depending on normality or skewed data). These correlation coefficients will be compared to see whether there is a difference in bone geometry between acute LAS or CAI patients.

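### Whether received treatment affects outcome is to be judged by an unadjusted Pearson or Spearman correlation in a cohort that does not allocate treatment

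*Protocol article*

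**What the plan says.** The analysis is described twice in the protocol article.

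- **Analyses, Additional analyses** gives the purpose: "the different treatments and symptoms during physical examination will be assessed for their relation to the functional outcome", with FAOS, CAIT and persisting instability as the outcomes. This is the language of association.
- **Data analysis and statistics, Additional analyses** gives the question and the method: "To assess whether the received treatment affects functional outcome and/or the progression to CAI will be assessed", followed by "Depending on normality of data the Pearson’s or Spearman’s rho will be used". The verb is now *affects*. No other method and no covariate is named.

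Four other places bear on it:

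- **Study design:** "This level II observational prospective cohort study, executed in 4 different Dutch hospitals". Patients receive standard care, and the study does not allocate treatment.
- **Follow-up:** treatment is recorded by questionnaire ("The questionnaires contain questions about patient characteristics, previous ankle sprains, treatment, restrictions and complaints"). No list, order or coding of the treatments is given.
- **Prognostic value of variables:** "a multivariate logistic regression will be performed to assess dependency between variables". This concerns the candidate predictors that pass univariate screening. Clinical outcome measures lists 16 of them, eleven radiographic and five patient characteristics. Treatment is not among them.
- **Data analysis and statistics:** a p-"value of < 0.05 is considered significant".

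**The concern.** Two features of the named method do not fit the question.

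First, a correlation coefficient needs numbers with an order. If the different treatments become one variable coded 1, 2, 3 and so on, the size, sign and p-value of Pearson's or Spearman's coefficient depend on which treatment gets which number. Choosing between the two by normality does not help, because neither a category code nor a yes/no CAI outcome is normally distributed.

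Second, and whatever the coding, the comparison is unadjusted. If patients with worse sprains tend to receive a particular treatment and also tend to develop CAI, the correlation reports their severity as if it were the treatment. The protocol accepts that care can vary with history: it says patients with earlier sprains "additionally may follow a different rehabilitation route due to familiarity with the complaints". Examination symptoms are collected, but they are analysed as a parallel exposure, not as covariates.

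At stake is the treatment conclusion. A difference could be missed through numbering, or a difference in severity could be published as an effect of treatment.

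**Working it through.** **The plan's own figures.** None is given for the treatment analysis. The model sample size reproduces: 20 events × 16 variables = 320 events; 320 / 0.30 = 1066.7 patients with outcome; 1066.7 / 0.90 = 1185.2, stated as 1185. The examples below use n = 1067 with outcome, CAI near 30% and a 0.05 level (two-sided assumed). Treatment shares, treatment risks and the severity link are assumptions, because the protocol gives none.

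**Check 1: dependence on numbering.** Assume three equal groups A, B and C with CAI risks of 25%, 40% and 25%. The mean is 0.30 and the outcome variance is 0.30 × 0.70 = 0.21. A code taking the values 1, 2, 3 has variance 2/3.

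- A=1, B=2, C=3: covariance = (−0.25 + 0 + 0.25)/3 = 0, so r = 0.
- A=1, B=3, C=2: covariance = (−0.25 + 0.40 + 0)/3 = 0.05, so r = 0.05 / √(0.21 × 0.667) = 0.13.
- Chi-square test on 2 df: noncentrality = 1067 × [(0.05² + 0.10² + 0.05²)/3] / 0.21 = 1067 × 0.005 / 0.21 = 25.4, whatever the numbering.
- Yes/no indicator for B: covariance = (1/3) × (0.40 − 0.30) = 0.0333, so phi = 0.0333 / √(0.222 × 0.21) = 0.15.

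| Analysis of the same data | Significant samples (simulated) |
|---|---|
| rho, numbered A-B-C | about 4% |
| rho, numbered A-C-B | about 99% |
| chi-square, 2 df | over 99% |
| phi, indicator for B | over 99% |

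The failure therefore belongs to a single multi-category code. It disappears with separate indicators.

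**Check 2: confounding by severity, no treatment effect.** Assume a normally distributed severity score S, logit P(treated) = bS (half treated) and logit P(CAI) = a + bS, with a set so that 30% develop CAI. Here b is the log of the odds ratio per SD, the same for treatment and for CAI. Treatment is a yes/no variable, so numbering plays no part.

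| Severity OR per SD | CAI risk, treated / untreated | Crude OR | Unadjusted correlation significant |
|---|---|---|---|
| 1.25 | 30.5% / 29.5% | 1.05 | about 7% |
| 1.5 | 31.6% / 28.4% | 1.2 | about 21% |
| 2 | 34.2% / 25.8% | 1.5 | about 84% |
| 3 | 38.4% / 21.6% | 2.3 | 100% |

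For the third row, the crude odds ratio is (0.342/0.658) / (0.258/0.742) = 0.520 / 0.348 = 1.49. The true odds ratio is 1 in every row. A regression that includes S rejects in about 5% of samples throughout.

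A second set-up, with binary severity (50% severe) and n = 1065, agrees. The unadjusted correlation rejects in 12% of samples when 40% of milder and 60% of severe cases are treated and CAI risks are 25% and 35%. It rejects in 81% when the shares are 30% and 70% and the risks 20% and 40%. The adjusted regression rejects in 4–5%. When treatment is unrelated to severity, the unadjusted correlation rejects in 5%.

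**The case against.** The defence has four parts, and each narrows the point.

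- **Coding.** A reader might infer that the coefficient is meaningless as planned. The protocol does not support that, because it never says how treatment is coded. With separate yes/no indicators, Pearson's r is a valid phi or point-biserial association, and a binary CAI outcome is no fault in itself. The numbering problem is conditional on a single code.
- **Severity.** A reader might infer that treatment was chosen by severity. No section says so. Patients are treated by standard protocol, the cohort is described as already limited to severe sprains, and Table 1 excludes surgery within 12 months of the emergency visit, which removes the contrast most likely to track severity. The remark about a different rehabilitation route concerns patients with earlier sprains, who are outside the primary analysis. This reduces the scope for confounding without removing it: standard care still includes different treatments, and nothing makes their allocation independent of prognosis.
- **Wording.** *Affects* is one verb in a garbled sentence, and the earlier description speaks only of a relation. That is fair, and it shows which wording to keep. It does not supply an adjustment.
- **Weight.** Treatment is absent from the study aim, the main objective and the candidate predictors. This stands, and it lowers the priority.

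The defence that such detail belongs in an analysis plan does not stand, because the protocol names the method itself.

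**Conclusion.** Wrong as written, for an additional analysis. The named method, an unadjusted correlation, does not answer whether a treatment that was not allocated affects outcome, and the regression planned elsewhere does not reach this question.

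The size cannot be fixed from the protocol. Under the assumptions shown, confounding ranges from negligible (crude odds ratio about 1.05, about 7% false positives at severity odds ratios of 1.25) to decisive (about 2.3 and 100% at odds ratios of 3). Quoting only the upper end would overstate what is known. The dependence on numbering, about 4% against 99% of samples significant on the same data, applies only if the treatments share one code.

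It would also go too far to conclude that the risk model or its validation is compromised. This analysis feeds neither of them, nor the sample size. What may be wrong is the reported treatment conclusion, so the priority is lower than for a fault in the primary model.

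**What to change.** In Data analysis and statistics, Additional analyses, replace the correlation for received treatment with logistic regression for CAI and linear regression for 12-month FAOS and CAIT. Enter treatment as a categorical factor, or as separate yes/no indicators if patients can receive more than one, and state which. Adjust for the examination findings and patient characteristics already collected. Replace *affects* with the associational wording used under Analyses, Additional analyses, and report the result as an adjusted association.

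The cost is a few sentences and slightly more modelling, with no new data. Adjustment covers only measured severity, so residual confounding must still be stated as a limitation.

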### Missing data

A per protocol analysis is applied based on patients filling out at least one questionnaire and having an available AP and lateral radiograph for radiographic assessment. In case the last questionnaire is missing, on which the diagnosis of CAI will be based, and the question concerning persisting complaints at six or twelve months is not answered, differentiation between full recovery or progression to chronicity cannot be made. For this reason these patients and patients with a missing radiograph will be excluded.

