### Study centres and participants

This study will be conducted at the ER of four Dutch hospitals: the AMC Amsterdam, Flevoziekenhuis Almere, Slotervaart Medical Center Amsterdam, VUmc Amsterdam. All subsequent patients that present themselves at the ER of one of the participating hospitals after an initial lateral ankle sprain will be treated according to standard protocol, including anamnesis, physical examination and (in case of positive Ottawa Ankle Rules (OAR)*) a radiograph [24]. When a mortise view and lateral radiograph is made and negative for ankle fractures or other joint pathology, patients are screened for eligibility according to the in -and exclusion criteria (Table 1).

**Table 1 Tab1:** Inclusion- and exclusion criteria

Inclusion criteria	Exclusion criteria
At least 16 years old	Present fracture or other joint pathology/bone matrix pathology
Visited the ER within one week after a lateral ankle sprain	A diagnosed OCD after primary inclusion
Agreed with being approached for this study	Medial ankle instability
Reported anterolateral ankle pain after an ankle sprain or ankle distortion	Previous ankle surgery
Filled out the baseline, 3-, or 6 month questionnaire; and the 12 month follow-up	An unreliable radiograph due to the angle in which it is made or low quality
	Acute surgical repair or the ATFL/CFL or any other form of surgery within 12 months after the ER visit

*Abbreviations*: *ER* Emergency Department, *AP* anteroposterior, *OCD* osteochondral defect, *ATFL* anterior talofibular ligament, *CFL* calcaneofibular ligament

*The OAR are a requirement at the ER according to Dutch protocols to conclude whether there is an indication for a radiograph. However, in cases of severe LAS patients there is a high risk at false positive OAR despite the absence of a fracture (due to a painful lateral malleolus with or without the ability to bear weight).

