### Definition CAI

Chronic ankle instability is defined as: *The perception of ‘giving-way’, in combination with a history of recurrent ankle sprains, the sensation of ankle instability and persistent disabilisty (pain, swelling* etc.*) that has not resolved in the time-frame from the first initial sprain up to the 12-months follow-up* [3, 25, 26]*.*

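### The missing-data rule implies that a six-month complaint answer can settle CAI status, contradicting the 12-month outcome fixed everywhere else in the methods

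*Protocol article*

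**What the plan says.** Four places in the protocol article fix the outcome at 12 months:

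- Definition CAI describes complaints "that has not resolved in the time-frame from the first initial sprain up to the 12-months follow-up".
- Study design states that "only the 12 month follow-up questionnaire is mandatory to diagnose CAI".
- Table 1 (Study centres and participants) lists as an inclusion criterion "Filled out the baseline, 3-, or 6 month questionnaire; and the 12 month follow-up". The Abstract gives the same requirement.
- Prognostic value of variables (under Analyses) relates each candidate factor to instability 12 months after the sprain.

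The Missing data section sets a different rule. It opens with "A per protocol analysis is applied based on patients filling out at least one questionnaire" and available radiographs, with no mention of a 12-month response. It then describes patients for whom recovery and chronicity cannot be told apart: the last questionnaire is missing and "the question concerning persisting complaints at six or twelve months is not answered". It concludes: "For this reason these patients and patients with a missing radiograph will be excluded".

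Two other places bear on the point. Under Follow-up, "one year after their ER visit they will be contacted, inquiring on persisting complaints and ankle instability", so there is a second source of 12-month information. The Discussion treats complaints that persist beyond six months as chronic instability already reached, which is a different time point from the definition.

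**The concern.** The exclusion has two conditions joined by 'and', and the second is met only when the complaint question is unanswered. A patient who skipped the 12-month questionnaire but answered that question at six months does not meet it and, by implication, stays in as recovered or chronic. Under Table 1 the same patient does not belong in the study.

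Two analysts, one following Table 1 and one following the Missing data section, would build different datasets with different event counts. In the second dataset, one complaint item at six months would stand in for a 12-month definition that combines giving way, recurrent sprains, a sensation of instability and persistent disability, and it would do so only for non-responders at month 12. A patient with complaints at six months who recovers by month 12 would be a false event.

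The recalculation of prevalence under PREDICT sample size counts patients who have returned the last questionnaire. The group that steers recruitment could therefore differ from the group analysed. The model is meant to support advice on surgery, so its outcome needs one unambiguous rule.

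**Working it through.** **1. The possible readings of the exclusion sentence**

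| Reading | Patient with a six-month answer and no 12-month data | Agrees with Study design, Table 1 and Definition CAI? |
|---|---|---|
| An answer at either time point is enough to stay in | Kept, classified from six months | No: outcome fixed at 12 months |
| Answers at both time points are needed to stay in | Excluded | Not with Study design, where only month 12 is mandatory |

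The first reading is the more natural one, and the Discussion's six-month notion of chronicity fits it. The one-year contact explains how a twelve-month answer can exist without the questionnaire. It does not explain why a six-month answer should be enough. Neither reading agrees with the rest of the methods, so the text has to change.

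**2. The plan's own sample size**

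Inputs (Table 2 and PREDICT sample size): 20 events per variable, 16 variables, 30% prevalence, 10% loss.

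- Events: 20 × 16 = 320
- Patients with an outcome: 320 / 0.30 = 1066.7
- Inflated for loss: 1066.7 / 0.90 = 1185.2, against 1185 stated. It reproduces.

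In this calculation the lost 10% contribute no events.

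**3. Illustration of false events per phase**

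Assumptions that are not in the documents: all lost patients answered at six months and none was reached at one year; 35–50% of them report complaints at six months; 20–40% of those recover by month 12.

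- Patients without 12-month data: 1185 × 0.10 = 118.5
- Counted as CAI from six months: 118.5 × 0.35 = 41.5 to 118.5 × 0.50 = 59.3
- False events: 41.5 × 0.20 = 8.3 to 59.3 × 0.40 = 23.7
- All counted events, including those added from six months: 320 + 41.5 = 361.5 to 320 + 59.3 = 379.3
- False share: 8.3 / 361.5 = 2.3% to 23.7 / 379.3 = 6.2%

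If only half of the 118.5 depended on the six-month answer and the other half were excluded:

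- Low end: 4.1 / (320 + 20.7) = 1.2%
- High end: 11.9 / (320 + 29.6) = 3.4%

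**4. A second illustration with other assumptions**

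True prevalence is 30%. A share f of analysed patients is classified at six months. All true CAI cases have complaints then, and so does a share q of the others.

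False share = 0.7fq / [0.3(1 − f) + f(0.3 + 0.7q)]

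- f = 5%, q = 25%: 0.00875 / 0.30875 = 2.8%
- f = 10%, q = 25%: 0.0175 / 0.3175 = 5.5%
- f = 10%, q = 50%: 0.035 / 0.335 = 10.4%

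**5. Effect of a strict 12-month rule on the sample size**

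At 1185 patients and 30% prevalence:

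- 10% loss: 1185 × 0.9 × 0.3 = 320 events, 20.0 per variable
- 20% loss (assumed): 284 events, 17.8 per variable
- 30% loss (assumed): 249 events, 15.6 per variable

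The planned number stands at the planned loss.

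**The case against.** The strongest defence is that the sentence only excludes. It nowhere says that a six-month answer will be scored as CAI, and it says itself that the diagnosis rests on the last questionnaire. The Abstract, Study design and Table 1 all require 12-month follow-up, Table 2 treats the lost 10% as contributing no events, and prevalence is recalculated on returned last questionnaires. On that view the six-month wording is a slip, and the one-year contact would catch most of the patients concerned. Much of this stands: retention is implied rather than stated, and the false-event figures depend on unsupported assumptions. It does not remove the contradiction, because no passage says which rule governs.

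A reader might infer three stronger points that the documents do not support:

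- **That the primary outcome is misclassified.** It can be, if the Missing data section is followed on its natural reading and such patients exist.
- **That dropping patients without an outcome necessarily biases the results.** It does so only if missingness is related to the outcome, and the documents give no evidence either way. For scale, with 30% CAI among those analysed and 10% excluded, overall prevalence is 0.9 × 0.30 + 0.1 × 0.10 = 28% if the excluded have 10% CAI, and 0.9 × 0.30 + 0.1 × 0.60 = 33% if they have 60%.
- **That accepting a 3- or 6-month questionnaire in place of baseline leaks outcome information into the predictors.** The eleven radiographic variables come from the emergency department films. Age, sex and height are not altered by instability, and sports intensity is described as the level the patient wants to return to. Only BMI is left, and nothing says that a later value replaces a missing baseline one. Table 1 only sets a minimum response.

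**Conclusion.** The contradiction holds and concerns how the primary outcome is ascertained. The Missing data section implies that a six-month answer can settle recovery or chronicity, while Definition CAI, Study design, Table 1 and the prognostic analysis fix the outcome at 12 months. The passages must be reconciled before the analysis dataset is built.

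The size of the consequence cannot be calculated from the documents. It depends on how many patients have only six-month information and how many of them recover later. About 2–6% of counted events would be false under the first set of assumptions in the working. The share would be lower if the one-year contact reaches these patients or if some did not answer at six months either, and higher if more of those who recover still had complaints at six months. The case for changing the text rests on the conflict between the rules, not on these percentages.

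**What to change.** Rewrite the Missing data section so that:

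1. CAI status comes only from 12-month information, meaning the 12-month questionnaire or the one-year contact already planned under Follow-up. Study design names only the questionnaire, so its wording should be aligned.
2. A six-month answer never defines the outcome.
3. The analysis set matches Table 1, replacing the requirement of at least one questionnaire.

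The Discussion's remark on complaints after six months should be worded so that it does not read as a second outcome definition.

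As a cheap addition, include a multiple-imputation sensitivity analysis beside the complete-case analysis. Restrict it to consenting patients who returned at least one questionnaire but lack 12-month status, and use the 3- and 6-month FAOS, CAIT and complaint answers as auxiliary variables. This uses the six-month information without treating it as the diagnosis. Extending imputation to people who returned no questionnaire would add almost no information and would reach patients whose consent is sought only at the questionnaire stage.

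The cost is amendment wording and some extra analysis work. The imputation relies on a missing-at-random assumption, which should be stated. No change to the 1185 per phase is needed at the planned 10% loss. If 12-month loss proves higher, events per variable fall as shown in the working, and the planned recalculation of the sample size should take that into account.
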